## Abstract

**Background:**

Radiotherapy has a good effect in palliation of painful bone metastases, with a pain response rate of more than 60%. However, shortly after treatment, in approximately 40% of patients a temporary pain flare occurs, which is defined as a two-point increase of the worst pain score on an 11-point rating scale compared to baseline, without a decrease in analgesic intake, or a 25% increase in analgesic intake without a decrease in worst pain score, compared to baseline. A pain flare has a negative impact on daily functioning and mood of patients. It is thought to be caused by periostial edema after radiotherapy. Dexamethasone might diminish this edema and thereby reduce the incidence of pain flare. Two non-randomized studies suggest that dexamethasone reduces the incidence of a pain flare by 50%. The aim of this trial is to study the effectiveness of dexamethasone to prevent a pain flare after palliative radiotherapy for painful bone metastases and to determine the optimal dose schedule.

**Methods and design:**

This study is a three-armed, double-blind, placebo-controlled multicenter trial. We aim to include 411 patients with uncomplicated painful bone metastases from any type of primary solid tumor who receive short schedule radiotherapy (all conventional treatment schedules from one to six fractions). Arm 1 consists of daily placebo for four days, arm 2 starts with 8 mg dexamethasone before the (first) radiotherapy and three days placebo thereafter. Arm 3 consists of four days 8 mg dexamethasone. The primary endpoint is the occurrence of a pain flare. Secondary endpoints are pain, quality of life and side-effects of dexamethasone versus placebo. Patients complete a questionnaire (Brief Pain Inventory with two added questions about side-effects of medication, the EORTC QLQ-C15-PAL and QLQ-BM22 for quality of life) at baseline, daily for two weeks and lastly at four weeks.

**Discussion:**

This study will show whether dexamethasone is effective in preventing a pain flare after palliative radiotherapy for painful bone metastases and, if so, to determine the optimal dose.

**Trial registration:**

This study is registered at ClinicalTrials.gov: NCT01669499

## Background

Radiotherapy, with a single fraction of 8 Gray as the gold standard, has a good effect in palliation of painful bone metastases, with a pain response rate of more than 60%. [1] However, a possible side-effect is a transient progression of pain, the so-called pain flare. This pain flare is defined as a two-point increase of the worst pain score on an 11-point rating scale, compared to baseline, without a decrease in analgesic intake, or a 25% increase in analgesic intake without a decrease in worst pain score. A pain flare is distinguished from progression of pain by requiring the worst pain score and analgesic intake to return to baseline levels after the flare [2].

Two prospective observational studies show that approximately 40% of patients experience a pain flare [3,4]. Hird studied 111 patients with uncomplicated painful bone metastases and showed an incidence of pain flare of 40%, with no difference between single or multiple fractions. The median duration of a pain flare was 1.5 days, while 25% of patients had more than one pain flare. Most of the pain flares occurred during the first five days after treatment. A pain flare occurred in 52% of patients with breast cancer and in 25% of patients with prostate cancer [3]. Loblaw studied 44 patients and found, with an adjusted, underestimating definition of a pain flare, an incidence of 41%, with a significant difference between single and multiple fractions (57% and 24% respectively) [4].

A survey among patients who experienced a pain flare showed that having a pain flare had a negative effect on daily functioning of patients and on their mood [5]. Most patients tried to manage their pain flare by increasing their pain medication, at the cost of possible side-effects. The majority of patients who experienced a pain flare stressed the need for prevention of this pain flare instead of managing it with breakthrough medication.

The pain flare is thought to arise through edema of the periostium of the irradiated bone. Dexamethasone, an anti-inflammatory drug decreasing edema, may be an effective drug. Two small studies were performed to study the effect of dexamethasone on the incidence of pain flare [6,7]. In the study by Chow a single dose of 8 mg dexamethasone was prescribed one hour before the single fraction radiotherapy. This study included 33 patients and showed an overall pain flare incidence of 24%. Most of the observed pain flares commenced after the half-life of dexamethasone [7], suggesting that a longer treatment time might be useful. Dexamethasone was well tolerated. A subsequent study, with 41 evaluable patients, used 8 mg dexamethasone before single fraction radiotherapy and then daily for three consecutive days. It showed an overall incidence of pain flare of 22%, with a median duration of one day [6].

Both studies concluded that randomized trials are necessary to study the effectiveness of dexamethasone for prevention of a pain flare. No randomized trials have been published so far. Therefore, the aim of this trial is to study the effectiveness of dexamethasone to prevent a pain flare after palliative radiotherapy for painful bone metastases and to determine the optimal dose schedule.

## Methods/Design

### Design

This three-armed, prospective, randomized, placebo-controlled multicenter study is being led by the University Medical Center Utrecht. The study is supported by grants from the Dutch Cancer Society and ZonMw. It is registered at ClinicalTrials.gov: NCT01669499. The study compares two different dose schedules of dexamethasone with a placebo (Figure 1). The aim is to study the effectiveness of dexamethasone to prevent the occurrence of a pain flare after radiotherapy for painful bone metastases and to define the optimal schedule of dosing. Secondary endpoints are pain scores, quality of life and side-effects of placebo and dexamethasone. In addition, the predictive value of a pain flare for response to the palliative radiotherapy will be studied.

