### Endpoints and analysis

Participating patients fill out a questionnaire at baseline (the start of treatment, defined as day 1), then daily until day 15 and a final questionnaire at day 29. The questionnaire contains the Brief Pain Inventory [8], which notes the level of pain on a 11 point pain scale ranging from 0 (no pain) to 10 (worst imaginable pain). Two questions are added about side-effects of the study medication (‘Do you have appetite?’ and ‘Do you feel restless?’). To assess quality of life, the EORTC QLQ-C15-PAL [9] and the EORTC QLQ-BM22 [10] are added (both at baseline, day 8, 15 and 29). Reminder telephone calls are performed twice during the study. The researchers contact participants who do not return their questionnaires. The occurrence of a pain flare, the primary endpoint of the study, is determined using the daily noted pain scores and pain medication. Pain response and side-effects of placebo and dexamethasone are assessed by the daily questionnaires.

Analysis will be by intention-to-treat. Patients who have received at least one fraction of radiotherapy, irrespective of study medication intake, and have returned questionnaires are evaluable. Descriptive analyses of baseline characteristics will be performed. Comparison of occurrence of pain flare between the three arms will be assessed using the Chi-Square test. Comparison of pain intensity, quality of life items and side effects at baseline and over time between the three arms will be done using multilevel analysis. Since the risks of the study using well-known medication are considered minimal, an interim analysis will not be performed.

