## Discussion

Up to 40% of patients experience a pain flare after palliative radiotherapy for painful bone metastases [3,4]. A pain flare severely impacts functional activity and mood of patients [5]. Therefore, it is clinically important to prevent the occurrence of a pain flare. Earlier publications suggest an effect of dexamethasone on the incidence of pain flare [6,7]. Although side-effects of a short course and relative low dosage of dexamethasone are considered minimal, the beneficial effect in this patient population should be proven before integrating dexamethasone medication into daily clinical radiotherapy practice. A prolonged schedule of dexamethasone might be better in preventing a pain flare. Therefore, in the present trial, we study different schedules, to be able to determine which one is the optimum schedule.

A recent publication from Chiang et al. (published after the initiation of our study) in patients treated with stereotactic radiotherapy for painful bone metastases showed an incidence of pain flare of 68%. However, this might be an overestimation. Firstly, they did not mention to require pain score and analgesic intake to return to baseline, to distinguish it from progression. Secondly, initiation of corticosteroids during or after treatment was considered to be indicative of a pain flare [11]. Nevertheless, these results give rise to the assumption that this group of patients might also benefit from our treatment results. However, the results of our study are not directly applicable to patients who are treated with stereotactic radiotherapy for painful bone metastases, since they represent a highly selected group of patients who receive much higher total doses of radiotherapy (e.g. 1 × 20 Gy, or 3 × 8 Gy).

Using consensus definitions of endpoints in literature is important, to be able to compare studies [12]. Most published studies concerning pain flare after palliative radiotherapy use the definition by Chow [2], incorporating pain scores, analgesics intake and returning to baseline to distinguish it from progression. Loblaw et al. [4] used a different definition for pain flare. They tried to convert it into the definition by Chow [2], but since they used a different pain scale, this was not completely possible, which made it difficult to interpret and compare these results with other published studies. We chose to also use the definition by Chow [2], to enable comparison with other studies.

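### Pain flare as a predictor of radiotherapy response: the flare definition requires a later return to baseline, which biases the association towards flare looking favourable

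*Protocol article*

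**What the plan says.** Under Design, after the secondary endpoints, the protocol article adds that "the predictive value of a pain flare for response to the palliative radiotherapy will be studied".

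The Background gives the two entry criteria for a flare: a two-point rise in worst pain, or a 25% rise in analgesic intake, each with a condition on the other measure. It then separates flare from progression by "requiring the worst pain score and analgesic intake to return to baseline levels after the flare". The Discussion describes the same published definition as "incorporating pain scores, analgesics intake and returning to baseline to distinguish it from progression" and says that this trial adopts it for comparability.

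Under Endpoints and analysis, flare "is determined using the daily noted pain scores and pain medication". The same section states: "Pain response and side-effects of placebo and dexamethasone are assessed by the daily questionnaires". Patients complete the questionnaire at baseline, "then daily until day 15 and a final questionnaire at day 29". Flare and response therefore come from one patient-reported record. The article gives no other flare definition for the predictor objective.

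**The concern.** A predictor should be fixed before the outcome it is meant to predict. Here an early rise becomes a flare only after the patient's later pain and analgesic use are known, and those later values also decide response. A patient whose pain rises and stays up is removed from the flare group by definition and is very probably a non-responder. The flare group is thus cleared of some of its failures.

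At stake is a false prognostic message: that a flare after radiotherapy signals a good response, when the early rise itself carries no such information or even points the other way.

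**Working it through.** **Plan's own figures.** The article gives no figure for this objective. Its total of 411 belongs to the primary endpoint, and it reproduces: 40% vs 20%, two-sided 5%, 90% power gives 109 per arm; 109/0.80 = 136.25, rounded up to 137; 3 × 137 = 411. It is used here only for the number evaluable, 411 × 0.80 ≈ 328.

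**Inputs.**
- Response R = 0.60. The Background says more than 60%.
- Early qualifying rise e = 0.40. The documents give 40% as the flare rate without dexamethasone; using it as the rate of any early rise is an assumption.
- No true association: early rise is independent of response.
- Responders who rise always return to baseline (assumption).
- q = share of non-responding early risers who return to baseline. The documents do not give it, so a range is shown.

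**Formulas.**
- Flare proportion: f = eR + e(1−R)q = 0.24 + 0.16q
- Response given flare: eR/f = 0.24/f
- Response given no flare, with non-returning risers counted there: (1−e)R/(1−f) = 0.36/(1−f)
- Non-returning risers as a share of all patients: e(1−R)(1−q) = 0.16(1−q)

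| q | f | Non-returning | Response, flare | Response, no flare | Odds ratio |
|---|---|---|---|---|---|
| 1.0 | 0.400 | 0% | 60% | 0.36/0.600 = 60% | 1.00 |
| 0.9 | 0.384 | 1.6% | 62.5% | 0.36/0.616 = 58.4% | 1.19 |
| 0.75 | 0.360 | 4% | 66.7% | 0.36/0.640 = 56.2% | 1.56 |
| 0.5 | 0.320 | 8% | 75.0% | 0.36/0.680 = 52.9% | 2.67 |

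**If non-returning risers are set aside.** The comparison group is then the never-risers, at 60%. The flare column does not change, so the contrasts are 62.5%, 66.7% and 75.0% against 60%. The bias is smaller but remains.

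**Sensitivity to e.** Response in the flare group does not depend on e. At q = 0.75 the no-flare figure is 57.5% for e = 0.30 and 54.5% for e = 0.50.

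**False-positive rate.** In 4,000 simulated trials of 328 patients under this null model, an uncorrected chi-square test at 5% rejected in 5.7%, 11%, 47% and 97% of trials for q = 1.0, 0.9, 0.75 and 0.5. With early rise alone as the predictor, resolved or not, rejection was between 4.4% and 5.7% throughout, and expected response is 60% in both groups.

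**Masking.** This is a separate illustration in which an early rise really is unfavourable. Assume 30% flares, 10% sustained rises that never respond, 60% response overall, and the same response rate in flares and never-risers: 0.60/0.90 = 66.7%. All early risers then respond at 0.30 × 0.667/0.40 = 50%, against 66.7% in never-risers. Flare versus no flare nevertheless shows 66.7% against (0.60 × 0.667)/0.70 = 57.1%, which reverses the sign. Setting the sustained risers aside gives 66.7% vs 66.7%, which hides the association.

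**The case against.** The best defence is that the article states this objective in one sentence. The comparison group, model, landmark and handling of arm may be in a full protocol or analysis plan that is not shown, and their absence is no finding. That is correct. In particular, the article does not say that progressors count as no flare; it only separates progression from flare. The point does not need that reading, because some bias remains under the null model when they are set aside.

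It can also be said that the objective concerns flare as conventionally defined, and that an early rise mixing flare with progression is a different predictor. This stands in part, and is a reason to report both. But whether a rise is flare or progression is known only once the later pain course has been seen, so the conventional flare cannot serve as an early predictor without this conditioning.

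Several stronger readings are tempting and are not supported:
- *The association is circular.* Return to baseline is not the same as response, so this is a bias and not a tautology.
- *Arm confounds the analysis.* That would follow if arms were pooled without adjustment, and the article does not say they will be.
- *The bias must be large.* It vanishes at q = 1, and no document gives q.
- *The primary result is compromised.* This mechanism does not touch the randomised comparison of flare rates.

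The Abstract omits the return condition, so a reader of it alone might take the predictor to be the rise itself. The Background and Discussion rule that out.

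**Conclusion.** The point holds for this additional objective. The stated definition alone creates the bias; it does not rest on missing detail. Under the null model the direction is fixed: flare looks favourable whenever non-responding risers return to baseline less often than responding ones. The definition exists to exclude rises that do not resolve, so it presumes that some occur.

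The size cannot be settled from the documents. With 60% response and a 40% early rise, the artefact is about 4 points at q = 0.9, 10 at q = 0.75 and 22 at q = 0.5, if non-returning risers are counted as no flare. It is 2.5, 6.7 and 15 points if they are set aside. At q = 0.75 only 4% of patients are misplaced. These figures rest on the assumptions that responders always return and that early rise is unrelated to response.

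**What to change.** For this objective only, define the predictor as any early qualifying rise (two points in worst pain, or 25% in analgesic intake, under the existing conditions) within a fixed early window set in advance, whether or not it resolves. Assess response after that window closes and adjust for arm. Changing only the response time, or only adjusting for arm, would not be enough, because non-returning risers would still be excluded from the flare group. Response should not simply be restricted to patients with day-29 data: with 20% drop-out assumed, that brings its own selection.

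The consensus-definition flare can be reported alongside for comparability, labelled as conditional on later return to baseline.

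The existing diaries supply the data, so nothing more is collected. The cost is some analysis wording and a second predictor under its own label. The primary endpoint, its definition and the sample size stay as they are.

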**Figure 1 F1:**
[figure not shown]
Treatment arms.

### Patients

The study includes patients with uncomplicated painful bone metastases from a solid tumor, who are referred for a short course of palliative radiotherapy. Short course radiotherapy encompasses all conventional treatment schedules from one to six fractions of radiotherapy. The full inclusion and exclusion criteria are listed in Table 1. Patients are randomized between the three treatment arms (Figure 1), after stratification for center and treatment schedule: single or multiple fractions. Randomization is performed by telephone at the Comprehensive Cancer Center The Netherlands. Double-blind randomization is guaranteed by only communicating the number of the medication box to patients and physicians.

**Table 1 T1:** Full inclusion and exclusion criteria

	
**Inclusion**	Patients of 18 years or older
	Uncomplicated painful bone metastases
	Primary malignancy is a solid tumor
	Pain intensity on a numeric rating scale of 2-8
	No immediately expected change in the analgesic regimen.
	Indication for single or short course radiotherapy
	Able to fill out Dutch questionnaires
	Able to follow instructions
	Informed consent provided
**Exclusion**	Patients with haematological malignancy
	Multiple sites to be irradiated
	Patients who have been treated before with palliative radiotherapy for painful bone metastases to the same bony localisation
	Current use of steroids (dexamethasone, prednisolone or other), use up to less than a week before randomization or expected use within 2 weeks after start of radiotherapy (e.g., as part of anti-emetic regimen for chemotherapy)
	Contraindications for the use of dexamethasone (to be judged by the radiation-oncologist)
	Long-term schedule radiotherapy (>6 fractions)
	Life expectancy shorter than 8 weeks
	Karnofsky performance score of 40 or less

### Ethics, informed consent and safety

The protocol has been approved by the medical ethics committee of the University Medical Center Utrecht. In the participating centers, local medical ethics committees have approved the protocol. The study is conducted in accordance with the Declaration of Helsinki. Written informed consent, signed and dated, is obtained before randomization. Serious adverse events (SAE) or suspected unexpected serious adverse reactions (SUSAR), as defined in the study protocol, are reported to the central medical ethics committee and to the central committee of medical research involving human subjects.

### Endpoints and analysis

Participating patients fill out a questionnaire at baseline (the start of treatment, defined as day 1), then daily until day 15 and a final questionnaire at day 29. The questionnaire contains the Brief Pain Inventory [8], which notes the level of pain on a 11 point pain scale ranging from 0 (no pain) to 10 (worst imaginable pain). Two questions are added about side-effects of the study medication (‘Do you have appetite?’ and ‘Do you feel restless?’). To assess quality of life, the EORTC QLQ-C15-PAL [9] and the EORTC QLQ-BM22 [10] are added (both at baseline, day 8, 15 and 29). Reminder telephone calls are performed twice during the study. The researchers contact participants who do not return their questionnaires. The occurrence of a pain flare, the primary endpoint of the study, is determined using the daily noted pain scores and pain medication. Pain response and side-effects of placebo and dexamethasone are assessed by the daily questionnaires.

Analysis will be by intention-to-treat. Patients who have received at least one fraction of radiotherapy, irrespective of study medication intake, and have returned questionnaires are evaluable. Descriptive analyses of baseline characteristics will be performed. Comparison of occurrence of pain flare between the three arms will be assessed using the Chi-Square test. Comparison of pain intensity, quality of life items and side effects at baseline and over time between the three arms will be done using multilevel analysis. Since the risks of the study using well-known medication are considered minimal, an interim analysis will not be performed.

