### Power calculation

Assuming a reduction of 50% (from 40 to 20%) of the occurrence of a pain flare by administering a single dose of 8 mg dexamethasone, a total of 411 patients are necessary (137 per arm) to reach a power of 90% given a significance level of 5% (2-sided), and assuming a drop-out of 20% during follow-up. In the Netherlands, around 3000 patients are eligible for this study yearly. With 12 out of 21 institutions participating and an estimated participation rate of 20%, the total study time needed is about 2 years.

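### The 90% power and 411 patients belong to one placebo versus single-dose comparison, while the named primary test spans three arms and by itself supports none of the pairwise conclusions sought

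*Protocol article*

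**What the plan says.** **Primary analysis** (Protocol article, Endpoints and analysis): "Comparison of occurrence of pain flare between the three arms will be assessed using the Chi-Square test". The section names no pairwise contrast, no order of testing and no gate.

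**Sample size** (Power calculation): the effect is "Assuming a reduction of 50% (from 40 to 20%) of the occurrence of a pain flare by administering a single dose of 8 mg dexamethasone". The result is "a total of 411 patients are necessary (137 per arm"), stated "to reach a power of 90% given a significance level of 5% (2-sided") and "assuming a drop-out of 20% during follow-up". No pain flare rate is given for the four-day arm.

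**Aims.** The Design section says: "The study compares two different dose schedules of dexamethasone with a placebo". The Background gives the aim as "to study the effectiveness of dexamethasone to prevent a pain flare after palliative radiotherapy for painful bone metastases and to determine the optimal dose schedule". The Discussion adds: "we study different schedules, to be able to determine which one is the optimum schedule".

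**The concern.** The article describes three different things. The power calculation concerns one pair of arms. The named test concerns the null hypothesis that all three arms have the same flare rate. The aims need conclusions on pairs: each schedule against placebo, and one schedule against the other.

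Rejecting equality of three proportions shows that at least one arm differs. It does not identify which one. To reach the stated aims the investigators must go on to pairwise tests, and the article does not say how these share the 5%. Depending on how that is done, the overall error rate is either kept or nearly doubled or more. The stated 90% is the power of a test that the analysis section does not name. The Discussion expects a positive result to change supportive care, so it should be fixed in advance what counts as a positive result, and for which schedule.

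**Working it through.** **Inputs.** From the Power calculation: 40% and 20%, two-sided 5%, power 90%, drop-out 20%, 137 per arm. From the Design section: three arms. The four-day flare rate is not given, so I assume a range of 15% to 40%.

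**1. Reproduce the stated size.** Pooled two-proportion formula, mean rate 0.30:

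n = [1.960·√(2·0.30·0.70) + 1.282·√(0.40·0.60 + 0.20·0.80)]² / 0.20² = (1.2702 + 0.8105)² / 0.04 = 108.2, so 109 evaluable per arm.

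109 / 0.80 = 136.25, so 137. Then 3 × 137 = 411, an exact match. The full 5% went to one contrast.

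**2. What a split of alpha would have needed, same formula.**

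| Alpha per test | Evaluable per arm | With drop-out | Total |
|---|---|---|---|
| 5% (as stated) | 109 | 137 | 411 |
| 2.5% (two tests) | 129 | 162 | 486 |
| 1.67% (three tests) | 140 | 175 | 525 |

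Power at the planned 109 per arm is Φ[(0.20 − z·√(0.42/109)) / √(0.40/109)]. This gives 90.2% with z = 1.960 (5%), 84.2% with z = 2.241 (2.5%) and 80.2% with z = 2.394 (1.67%).

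**3. Familywise error with no true difference.** Simulation, 109 evaluable per arm, 400,000 trials per setting, common flare rate 20%, 30% or 40%:

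- two placebo comparisons at 5% each, no gate: 8.6–9.3%
- all three pairs at 5% each, no gate: 11.6–12.5%
- each pair at 5%, but only after a significant three-arm test: 5.0–5.1%

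The last result is expected. With exactly three arms, if any two pairwise nulls are true then all three arms are equal, so the three-arm test followed by pairwise 5% tests is a closed procedure.

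**4. Power by four-day rate.** Same simulation, placebo 40%, single dose 20%:

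| Four-day rate (assumed) | Three-arm test | Single dose vs placebo, gated |
|---|---|---|
| 15% | 98.5% | 90% |
| 20% | 94% | 89% |
| 25% | 87% | 85% |
| 30% | 84% | 83% |
| 35% | 87% | 85% |
| 40% | 93% | 88% |

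The power of the named test thus depends on a rate that the article does not state. It is lowest when the four-day arm lies midway between the other two.

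**5. One schedule against the other.** At 109 per arm and unadjusted 5%, power is about 16% for 20% versus 15% and about 54% for 20% versus 10%. For the rates seen in the two small studies cited in the Background (24% and 22%), it is barely above the 5% level itself.

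**The case against.** The strongest reply is that the three-arm test is a sound first step. It holds 5% by itself, and pairwise 5% tests that follow only if it rejects also hold 5%. A reader might infer that any move from the three-arm test to pairwise tests inflates the error; step 3 shows that it does not. The 9% and 12% apply only to pairwise tests run without the gate, and the article does not say that this is planned. The analysis sentence could be read as meaning separate pairwise chi-square tests. Those figures would then apply unless a rule stands elsewhere.

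A reader might also infer that the trial has no multiplicity control at all. That cannot be said. The article condenses a fuller protocol, and neither that protocol nor an analysis plan is shown; a rule may stand there. Nor does it follow that 411 is miscalculated or that the three-arm test is generally underpowered. The arithmetic is exact, and that test exceeds 90% when the four-day rate is 20% or lower, or equal to placebo. Sizing on one key contrast is common practice.

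All of this stands, and it limits the point. It does not remove the mismatch: the power statement and the analysis statement in this article concern different tests, and the named test does not answer the questions that the article sets.

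**Conclusion.** The concern holds in a limited form. The 90% and the 411 are right for one unadjusted comparison of placebo with the single dose. They are not the power of the named three-arm test, which runs from about 84% to 98.5% as the four-day rate varies over 15–40%. That test alone cannot support a claim for either schedule or a choice between them.

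The size of the error problem depends on the unstated next step: about 9% or 12% for ungated pairwise tests, 5% for gated ones. The figures assume 109 evaluable per arm, equal allocation, Pearson chi-square without continuity correction, and the article's 40% and 20%. The conclusion is confined to this article.

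**What to change.** Make the pairwise contrasts the stated primary claims, under one rule, and restate power for that rule. Two rules fit the planned size.

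- **(a) Gate.** Three-arm chi-square at two-sided 5%; only if it rejects, test each pair at 5%. State the assumed four-day rate, and give power for single dose versus placebo as a range of about 83–90% (about 89% at 40/20/20, about 83% at 40/20/30, in the order placebo, single dose, four-day).
- **(b) Fixed sequence.** Placebo versus single dose first at 5%, then the other contrasts in a named order, each at 5% and only while every earlier one is significant. This keeps the stated 90% for the first contrast.

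With either rule, add that the comparison of the two schedules has low power (about 16% unadjusted for 20% versus 15%), so a non-significant difference must not be read as equivalence.

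Cost: a few sentences in the analysis and power sections, settled before unblinding, and no extra patients. Under (a) the stated power is somewhat less favourable, by up to about 7 points (90 − 83). Under (b) no later contrast can be claimed if the first fails. A plain alpha split is also valid, but at the planned size it gives about 84% power for two tests or 80% for three; keeping 90% would take 486 or 525 patients.

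### The primary chi-square test ignores the fractionation stratum used in randomisation; if fractionation is prognostic, the test is mildly conservative and gives up a little power

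*Protocol article*

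**What the plan says.** The Patients section of the protocol article allocates patients to the three arms "after stratification for center and treatment schedule: single or multiple fractions". The Endpoints and analysis section names the primary test: "Comparison of occurrence of pain flare between the three arms will be assessed using the Chi-Square test". No stratum or covariate enters that test.

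The Background gives two cohorts on fractionation, and they disagree. The 44-patient cohort, which used an adjusted flare definition, is reported "with a significant difference between single and multiple fractions (57% and 24% respectively". The 111-patient cohort is reported as showing no difference between single and multiple fractions.

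The Power calculation section starts from "Assuming a reduction of 50% (from 40 to 20%) of the occurrence of a pain flare", asks for 90% power at a two-sided 5% level with 20% drop-out, and arrives at 137 patients per arm.

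**The concern.** Stratified randomisation balances the arms on fractionation. If fractionation predicts flare, that balance removes part of the chance variation in the difference between arms. The ordinary chi-square does not credit this, because its variance comes from the pooled flare rate as though patients were one homogeneous group. The test then rejects less often than its nominal 5% under the null, and an interval built on the same variance is wider than the design warrants. The trial would pay for stratification at randomisation and not collect the benefit in the analysis.

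A related point concerns interpretation. The Background describes both dexamethasone pilot studies as given before single-fraction radiotherapy, while this trial admits one to six fractions and assumes one effect for all. The trial randomises within the multiple-fraction stratum, so it can describe the effect there, but a pooled test does not.

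**Working it through.** **Inputs from the documents.** Flare rates 40% and 20%; two-sided 5%; power 90%; drop-out 20%; 137 per arm; control rates by fractionation of 57% and 24% (44-patient cohort) or no difference (111-patient cohort).

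**Assumptions not in the documents.** The share of single-fraction patients (even split unless stated), the same relative reduction in each stratum, and arms exactly balanced on fractionation among evaluable patients. Drop-out will loosen that balance somewhat, so the losses below lean towards the upper end.

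**1. The plan's own figure.** With pooled variance and no continuity correction,

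n = [1.960·√(2·0.3·0.7) + 1.282·√(0.4·0.6 + 0.2·0.8)]² / 0.2² = 108.2, so 109 per arm.

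109/0.8 = 136.25, so 137 per arm; 3 × 137 = 411. The stated total reproduces exactly, from an unstratified comparison of two arms.

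**2. Null variance, 57%/24%, even split.**
- Pooled rate: (0.57 + 0.24)/2 = 0.405.
- Variance per patient used by the plain test: 0.405 × 0.595 = 0.2410.
- Variance that applies within strata: (0.57 × 0.43 + 0.24 × 0.76)/2 = 0.2138.
- Ratio of standard errors: √(0.2410/0.2138) = 1.062, so the null standard error is about 6% too large.
- Approximate type I error: 2·[1 − Φ(1.96 × 1.062)] = 3.7%.

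Simulation with 109 per arm gives 3.5% for the plain pairwise chi-square and 5.0% for Cochran-Mantel-Haenszel (CMH). The three-arm chi-square, simulated with 110 per arm and a 48.5% single-fraction share, also runs at about 3.5%.

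**3. Interval width at the planned 50% reduction (treated rates 28.5% and 12%).**
- Treated arm, pooled: 0.2025 × 0.7975 = 0.1615.
- Treated arm, within strata: (0.285 × 0.715 + 0.12 × 0.88)/2 = 0.1547.
- Ratio of widths: √[(0.2410 + 0.1615)/(0.2138 + 0.1547)] = 1.045.
- With 137 × 0.8 = 109.6 evaluable per arm, the 95% half-width is 11.9 points unstratified and 11.4 stratified.

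**4. Power, placebo against one dexamethasone arm (simulated, 109 per arm).**

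| Relative reduction | Plain chi-square | CMH |
|---|---|---|
| 50% (planned) | 91.9% | 92.9% |
| 40% (assumed) | 73.8% | 76.1% |

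**5. Sensitivity to the single-fraction share, 50% reduction.** At a 30% share the interval is 4.2% too wide and stratifying gains 1.7 power points. At 90% the figures are 1.4% and 0.1 points. The excess width peaks at about 4.5% near an even split.

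**6. No difference by fractionation.** The pooled and within-stratum variances coincide, so the interval is 0% too wide. Simulated power at 40% against 20%, with 110 per arm, is 90.5% with either test.

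**7. Centre.** The article gives no flare rates by centre, so the effect of ignoring centre cannot be computed.

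**The case against.** The strongest reply is that fractionation is not established as prognostic. The 57% and 24% come from 44 patients, under a flare definition that the article itself calls adjusted and hard to compare. The larger cohort found no difference. This stands: the loss is conditional and may be nil.

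It is also fair that nothing here threatens validity. Any error is on the conservative side, the randomised comparison is unbiased, and the 411 was derived for an unstratified comparison, so the plan is consistent with itself on power. Covariate lists and subgroup detail commonly belong in a full protocol or analysis plan, neither of which is shown, and their absence from an article is no finding. What remains is that the article does name its primary test, and that test does not use the strata named at randomisation.

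Two stronger readings are tempting:

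- **Primary tumour.** The Background reports that "A pain flare occurred in 52% of patients with breast cancer and in 25% of patients with prostate cancer", and a reader might infer that ignoring tumour type makes the test more conservative still. It does not, because tumour type is not a stratification factor. Its chance imbalance is part of the variation that the plain test already allows for. Adjustment would only gain precision: the interval would be about 6 to 7% narrower with fractionation and tumour type together, under assumed even splits.
- **Effect by fractionation.** A reader might fault the primary test for not showing whether the benefit extends to multiple fractions. A CMH test would not show it either; that needs a separate estimate in each stratum.

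**Conclusion.** The mismatch between a stratified design and an unstratified primary test is real, and its direction is clear: conservative if fractionation matters, harmless if it does not. Across the two cohorts in the Background, the 95% interval is between 0% and about 4.5% too wide, and pairwise type I error lies between its nominal 5% and about 3.5%. The power lost at the planned effect is nil to about 1 point near an even split, and at most 1.7 points over the shares examined. It is about 2 points if the reduction is only 40%.

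These figures rest on the assumed stratum shares, a constant relative reduction and balance among evaluable patients. This is a modest efficiency point that is worth taking because it is nearly free. It gives no reason to doubt the trial's validity or to change its sample size.

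**What to change.** - Make the primary test a Cochran-Mantel-Haenszel test stratified by single versus multiple fractions. Include centre as well where feasible, with small centres pooled.
- Report the stratified risk difference with its 95% confidence interval.
- Keep the plain chi-square as a supportive analysis.
- Optionally, give the arm effect within each fractionation stratum as a descriptive secondary estimate, since both pilots used single-fraction radiotherapy.
- Adjustment for primary tumour is optional. A covariate-adjusted logistic regression would be a different analysis with a different estimand, not an equivalent of the stratified test. The article also does not state that primary tumour is recorded.

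The cost is a change of analysis wording, to be made before unblinding. Fractionation and centre must be known at randomisation, so no new data are needed and 411 patients remain sufficient under the plan's own assumptions. If fractionation proves not to be prognostic, stratifying costs essentially nothing.
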